### Sample size

Sample size for the primary outcome (proportion with PIP) is based on a prevalence of approximately 40% for PIP in this population [7]. To reduce this to 20% requires a sample size of 240 patients. The sample size also needs to be adjusted to reflect the assumption that individual outcomes are not independent of each other, as participants in the same cluster may respond in the same way. Hence, an intra-cluster correlation coefficient (ICC) of 0.025 will be used. This was also used in the OPTI-SCRIPT study and was based on an observational study of an elderly cohort in the HRB Centre for Primary Care Research [49]. This gives a design effect size of 1.35, thus inflating the sample to 324 patients from 22 practices. An equal cluster size of 15 patients per practice has been assumed.

All the patients in this study will be selected on the basis of receiving 15 or more repeat medicines on their prescription. Existing data from the Irish national prescribing database (HSE-PCRS) highlights that in those aged 65 years and over on 15 or more repeat medicines, the mean number of medicines is 17.4 (SD 2.69) [7]. A meta-analysis of deprescribing trials reported a difference between treatment groups of 0.4 medicines where the mean number of medicines was 7.4 [50]. We are targeting patients on at least 15 repeat medicines and for primary outcome, number of repeat medications, will test for a mean difference of one medicine between the intervention and control group and this would require a sample size of 306 patients. This is inflated by the design effect size outlined above (1.35) to give a sample of 413 patients from 28 practices.

Factoring in a loss to follow-up of approximately 10% (for primary outcomes, based on chart data) and using the higher numbers required to demonstrate a significant reduction in mean number of repeat medicines, a total of 30 GP practices and 450 patients will be required.

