### Results

The feasibility of the finder tool and intervention were assessed through GP feedback and analysis of use of the online material. Overall, the intervention was well received by the GPs and their patients many of whom reported feeling reassured that their medicines were being reviewed and rationalised. There was a large variation between practices in the proportion of those aged ≥65 years detected by the finder tool (1.9–17%) which may be partially explained by differences between practices in how prescription lists are kept up to date and socio-demographic differences, both of which will be identified by the practice profile questionnaire at baseline for the main trial. Due to lack of universal registration of private patients in Irish general practice, practices use varying approaches to count their private patient panel. The differences in the finder tool detection rate may also reflect an inaccurate denominator, where private patients aged ≥65 years are over counted for example visitors and those who have moved.

Of the 10 patients who underwent the medication review, they were prescribed an average of 17.5 medicines (SD +/−3.41) and this reduced to 16.8 (SD +/−3.94) immediately post-intervention. All of the included patients had at least 1 PIP, with a mean of 1.8 per patient. The most common PIP identified were the use of a “proton pump inhibitor for uncomplicated PUD/erosive peptic oesophagitis at full therapeutic dose for ≥8 weeks” (39%) and the use of a “benzodiazepine or Z drug for longer than 4 weeks” (39%). When the higher prevalence, lower risk proton pump inhibitor PIP was excluded, 90% of patients had at least 1 PIP and the mean number of PIP per patient was 1.1. Identified instances of PIP were acted on in 44% of cases and 45% when the proton pump inhibitor PIP was excluded. The most commonly reported patient treatment priorities were treating pain, followed by fatigue and reducing the number of repeat medicines.

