### Recruitment and allocation

Eligible practices (see eligibility criteria above) will be identified through the Health Research Board Primary Care Clinical Trials Network, Ireland (http://primarycaretrials.ie/) and invited to participate by formal letter, including letter of agreement to participate and study information leaflets detailing the steps of the intervention. Practices will identify patients aged 65 years and over who are currently prescribed 15 or more repeat medicines using the patient finder tool, which will be integrated into practice management software in participating practices. The research team will assist practices in recruiting eligible patients, who will be sent invitation letters (on practice headed paper) with consent forms, information leaflets and questionnaires. Based on recent analysis of prescribing trends in Ireland, we anticipate that most included practices will have at least 15 eligible patients [7]. In larger practices with more than 40 eligible patients, we will randomly select 40 patients to invite, based on the OPTI-SCRIPT response rate [28]. Control practices will receive €30 per recruited patient and intervention practices €60 per recruited patient to reflect some of the costs involved in taking part in the study.

Baseline data collection will occur prior to practice allocation by review of patient prescriptions and questionnaires (see outcomes and methods for data collection below). Recruited practices will be randomly allocated, using minimisation and randomisation software, by an independent third party (Fig. 2). Minimisation will ensure balance between the groups [39, 40] in terms of practice size (number of whole-time-equivalent GPs) and location (urban versus rural). An “urban” practice is defined as being located in an area with a population of at least 5000 people, has most of its patients within a relatively small geographical area and have ready access some hospital facilities [42]. Considering the nature of the intervention, it is not possible to blind GPs or participants to the intervention.

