### Outcomes measures

Outcome measures pertain to the individual patient level and have been specifically chosen to reflect the potential effects of the intervention and to incorporate the patient perspective. Baseline data will be collected prior to allocation using the PMS, patient questionnaires and a practice profile questionnaire. Follow-up data will be collected 6 months following completion of each medication review in intervention patients through review of the PMS and patient questionnaires and 6 months following the median date of all the medication review dates in control practices.

*Primary outcomes:*
Proportion of patients with any PIP (see Tables 2, 3, and 4)Mean number of repeat medications, defined as any medicine with an ATC code for which the patient is currently in receipt of a repeat prescription.

*Secondary outcomes:*
Reduction in proportion of patients with 15 or more medicines (100% at baseline)Medication changes○ Number of medications stopped (per patient and absolute number in intervention versus control)○ Numbers of medications started (per patient and absolute number in intervention versus control)○ Reduction in the number of PIP (per patient and absolute number in intervention versus control)○ Proportion of patients with any reduction in PIP
Multimorbidity Treatment Burden Questionnaire (MTBQ) [44]Health related quality of life (EQ5D-5L) [45]Revised Patients’ Attitudes Towards Deprescribing (rPATD) [46]Health service utilisation per patient (based on chart data and collected on both time periods (baseline and 6 months post-intervention completion), at study completion by the research team○ Number of GP/practice nurse visits○ Number of out-of-hours visits○ Number of Accident & Emergency (A&E) visits○ Number of emergency hospital admissions and reason for admission○ Number of in-patient days○ Number of out-patient visits
Patient-reported adverse drug withdrawal events (ADWEs) from follow-up patient questionnaire (defined as either recurrence of the condition for which the drug was prescribed or a physiologic reaction to drug withdrawal.) [47, 48]

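### The sample size for number of repeat medicines uses the SD of an entry distribution cut off at 15, although the outcome is the 6-month count, and the stated model carries no baseline count to offset a wider spread

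*Protocol article*

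**What the plan says.** In the protocol article, Sample size, the number of medicines is planned from national dispensing data: "in those aged 65 years and over on 15 or more repeat medicines, the mean number of medicines is 17.4 (SD 2.69"). The trial "will test for a mean difference of one medicine between the intervention and control group", and "this would require a sample size of 306 patients". A design effect of 1.35 (15 patients per practice; "an intra-cluster correlation coefficient (ICC) of 0.025 will be used") raises this to 413 patients from 28 practices. After a loss of approximately 10%, "a total of 30 GP practices and 450 patients will be required". The section says the final size follows the larger of the two primary-outcome calculations, which is this one. It gives no alpha, power or SD for the follow-up count.

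Outcomes measures places follow-up 6 months after the medication review. It lists as a secondary outcome "Reduction in proportion of patients with 15 or more medicines (100% at baseline"), so the entry floor of 15 is expected to be crossed. Plan of analysis specifies a Poisson regression with practice as random effect and names no covariate.

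The pilot study Results give, for 10 patients, a mean of 17.5 medicines (SD 3.41) before review, "and this reduced to 16.8 (SD +/−3.94) immediately post-intervention".

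**The concern.** The sample-size formula needs the spread of the outcome in the comparison to be made. The value used is the spread at entry, in a group with everyone below 15 removed. Six months later that floor is gone, and starts and stops have added variation of their own, so the spread of the follow-up count is likely to be wider than 2.69. The only other SDs in the article, from the pilot, are both above 2.69, and the later one is the larger.

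A baseline covariate would remove much of the extra spread, but the model as described contains only the practice effect. This outcome sets the number of practices and patients, so an SD that is too small lowers the power of the calculation that sizes the whole trial.

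**Working it through.** **Inputs.** Difference 1 medicine, SD 2.69, ICC 0.025, cluster size 15, loss about 10%, final size 450 (all from Sample size). Pilot SDs 3.41 and 3.94, n = 10 (pilot Results). Assumed: equal allocation (the ratio is not stated; Recruitment and allocation says "Minimisation will ensure balance between the groups"). Inferred: two-sided 5% and 90% power.

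**Reproducing the plan's figures.**

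- n per arm = 2 × SD² × (1.960 + 1.2816)² / 1² = 2 × 7.236 × 10.507 = 152.1, rounded up to 153, or 306 in total. This matches. At 80% power the total would be 228, and one-sided at 90% it would be 248, so neither matches.
- Design effect = 1 + (15 − 1) × 0.025 = 1.35. 306 × 1.35 = 413.1, and 413/15 = 27.5, so 28 practices. This matches.

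**Varying the SD, unadjusted comparison.** Power = Φ(1 / (SD × √(2/153)) − 1.96). The last column is the baseline correlation that brings the residual SD back to 2.69: r = √(1 − (2.69/SD)²).

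| 6-month SD | Source | Power at effective n 306 | n for 90% power | × 1.35 | r needed |
|---|---|---|---|---|---|
| 2.69 | plan | 90% | 306 | 413 | – |
| 3.0 | illustration | 83% | 380 | 513 | 0.44 |
| 3.11 | 2.69 × 3.94/3.41 | 80% | 408 | 551 | 0.50 |
| 3.41 | pilot, before review | 73% | 490 | 662 | 0.61 |
| 3.94 | pilot, just after review | 60% | 654 | 883 | 0.73 |

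The 3.11 row takes only the relative widening from the pilot and keeps the national entry SD. The last two rows take the pilot SDs at face value.

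**How far the SD might move (assumed slopes and residual SDs).** Follow-up SD = √(slope² × 2.69² + residual SD²).

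- Slope 1.0, residual SD 2: √(7.24 + 4) = 3.35.
- Slope 0.8, residual SD 2: √(0.64 × 7.24 + 4) = 2.94.
- Slope 0.7, residual SD 2: √(0.49 × 7.24 + 4) = 2.75.

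**Power with baseline adjustment**, at 405 analysed (effective n 405/1.35 = 300): SD 3.41 with r = 0.7 gives 94%. SD 3.94 gives 87% with r = 0.7 and 72% with r = 0.5.

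**Loss to follow-up.** 413/0.9 = 459, while 450 × 0.9 = 405, and 1 − 413/450 = 8.2%. With the design effect held at 1.35, effective n is 300 and power at SD 2.69 is 89.6%. If loss is spread across practices, cluster size becomes 13.5, the design effect 1 + 12.5 × 0.025 = 1.3125, effective n 405/1.3125 = 308.6, and power 90.4%.

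**The case against.** Nothing in the arithmetic is wrong: 306, 1.35, 413 and 28 all reproduce, and the source of the SD is declared. Using a target-population SD for a follow-up count is a planning assumption, not a contradiction. That stands. What can be criticised is that the assumption goes unexplained when the outcome and the pilot both point to a wider spread.

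A reader might infer that the 6-month SD must exceed 2.69. The documents do not support that. Patients selected for a high count tend to regress towards the mean, and with a slope of 0.7 and residual SD of 2 the follow-up SD is only about 2.75. Likely larger is as far as one can go.

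A reader might also take 60% power, or a need for some 880 patients, as the finding. The pilot has 10 uncontrolled patients and its second measurement is immediate, not at 6 months. The 95% confidence interval for the SD of 3.94 runs from about 2.7 to 7.2. Its pre-review SD of 3.41 is already above 2.69 in patients targeted at 15 or more, so that gap is not an effect of truncation. Only the widening from 3.41 to 3.94 bears on the point, and scaled to 2.69 it gives about 3.1.

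The article is condensed and covariates are commonly left to the analysis plan, so an unlisted baseline term does not show that the analysis will be unadjusted. This stands too: the power figures above are conditional on an unadjusted comparison. Nor does the article state a power that is then missed; 90% is implied by 306.

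Finally, a reader might infer that 450 fails because 405 is below 413. The loss is given as approximate, and power is 89.6% to 90.4% depending on how the design effect is handled. That is no defect.

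**Conclusion.** The point holds in limited form. The calculation that sets the trial's size rests on an SD from a distribution truncated at entry, while the outcome is a 6-month count that is not truncated and is likely to be more variable. The article offers no 6-month SD and no reason why 2.69 should carry over.

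If the comparison is unadjusted, the implied 90% power is about 80% to 83% for a 6-month SD of 3.0 to 3.1. It is 73% at 3.41 and 60% at 3.94, but those two values rest on the small pilot and should be read as a pessimistic end, not an estimate. The range assumes equal allocation, two-sided 5%, a one-medicine difference and an effective n of 306. With baseline adjustment the present size can be adequate, provided the correlation is about 0.5 (for SD 3.1) to 0.73 (for SD 3.94). The documents give no correlation, so this too is an assumption.

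**What to change.** - Name the baseline number of repeat medicines as a covariate in the primary model for this outcome. It is collected before allocation, so no new data are needed.
- Restate the sample size on a range of 6-month SDs (for example 3.0 to 3.94), with the assumed baseline correlation and the alpha and power used.
- State how standard errors are obtained. An ordinary Poisson model sets the variance equal to the mean, an SD of √17.4 = 4.17 at the planning mean, and baseline adjustment does not shrink model-based errors of that kind. The gain assumes errors that follow the actual spread, such as robust errors or an estimated dispersion.
- Optionally, describe the loss allowance as about 8%, or show the calculation with the reduced cluster size of 13.5.

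The cost is rewording of Sample size and one added term in Plan of analysis. No extra patients or practices are needed if the assumed correlation holds. The power shown for an unadjusted comparison would be less favourable than 306 now implies.

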### Process evaluation

SPPiRE is a complex intervention as there are several different interacting components and a degree of flexibility or tailoring to the local environment [31]. The aim of the process evaluation will be to explore the effect of the intervention and how it was implemented. It will combine both quantitative and qualitative data and follow a framework specific for cluster RCTs [51].

### Study population

All participating practices and a purposive sample of patients will be invited to participate by letter and follow-up telephone call.

### Process evaluation data collection

Quantitative data will be compiled from a number of sources including completed questionnaires, researcher logs and evaluation forms and website usage data. Qualitative data will be collected from patients and GPs and other practice staff using semi-structured interviews. The number of interviews needed to reach data saturation (where no new themes emerge) will be considered alongside feasibility issues (resources and timing), but a sample of 15–20 is proposed [45].

These interviews will be conducted either in person or via telephone. Telephone interviewing is generally used where time or costs are issues, and evidence suggests there is little difference in the answers obtained this way [52]. All interviews will be audio recorded (on loud speaker for telephone interviews).

Process evaluation measures:Use of the intervention softwareClinical/ prescribing decision made, e.g. stop or start medicine, refer for monitoring blood testReported primary reason for decision made, e.g. risks outweigh benefits, patient preference, hospital/consultant initiatedWhether assessment of patient priorities resulted in medication change and which priorities were associated with most changeImmediate pre- and post-intervention prescription

### Process evaluation data analysis

Quantitative data will be summarised using descriptive statistics. All interviews will be transcribed verbatim and broad themes and sub-themes identified using thematic analysis. NVivo 10 (QSR International) will be used to assist with organising the data for analysis.

### Economic evaluation

The health economic analysis will consist of a trial-based economic evaluation of the proposed intervention and will incorporate both cost effectiveness analysis and cost utility analysis. The evaluation will be undertaken in a manner consistent with guidelines issued by the Health Information and Quality Authority (HIQA) in Ireland [53]. Evidence collected on resource use, costs and health outcome measures will provide the basis for the evaluation over the trial follow-up period. With respect to costing, a publicly funded health service perspective will be adopted. That is, resource use associated with delivery of the proposed intervention will be measured and costed, as will other health service resource use by patients over the course of the trial. As detailed above, significant attention will be paid to collecting relevant data on health outcomes alongside the trial for the purposes of the clinical effectiveness analysis. For the cost effectiveness analysis, effectiveness will be evaluated on the basis of the number of PIPs averted. For the cost utility analysis, effectiveness will be evaluated in terms of quality adjusted life years (QALYs), which will be estimated based on responses to the EuroQol EQ-5D-5L instrument [45]. An incremental analysis will be undertaken to provide information on the marginal costs and effects of the intervention relative to the control through the calculation of incremental cost effectiveness ratios (ICERs). The statistical analysis will be conducted in accordance with current guidelines for economic evaluation alongside cluster RCTs [53]. That is, we will adopt multilevel statistical techniques which recognise both the clustering and correlation in the cost and effect data. Uncertainty in the economic analysis will be addressed by estimating cost effectiveness acceptability curves (CEACs), which link the probability of treatment being cost effective to a range of potential threshold values (λ) that a health system may be willing to pay.

### Data management and protection

All patients will provide informed consent and will be known to the research team by study ID only. The patient’s GP remains responsible for all treatment decisions made. Informed consent will be sought from all GPs participating in the study. All data collected, including interview transcripts for the process evaluation, will be stored on a secure, password protected network drive.

### Monitoring and participant safety

A Trial Steering Committee (TSC) comprising an independent chair and two other independent members, one of whom is a lay member representing the patient and public perspective, has been established and will oversee the progress of the trial and adherence to the study protocol. It was agreed by the TSC that given the low risk nature of the trial, lack of interim data and relatively short term follow-up, that there is no need for the establishment of a Data Monitoring Committee.

A formal process has been developed to capture any potential adverse events related to discontinuing medication. Recruited practices will be instructed in the practice recruitment leaflet on how to report any suspected adverse effects from deprescribing. Any adverse events will also be captured by a chart review at follow-up data collection. An assessment on likely causality will then be made using an adapted drug withdrawal probability scale [48]. Patient-reported ADWEs will also be collected as a secondary outcome measures in the follow-up patient questionnaire, 6 months after intervention completion. Any patient safety concerns arising during the course of the trial, including at baseline data collection, will be brought to the attention of the Trial Steering Committee.

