## Discussion

Polypharmacy is frequently cited as an area of major concern by patients with multimorbidity [54, 55]. The most appropriate course of action when deciding whether to continue to prescribe is often not readily apparent but should include some assessment of the relative harms and benefits of treatment, in the context of the patient’s priorities [56]. We propose that an individualised structured medication review, where deprescribing is considered alongside prescribing, and where there is active engagement with patients on their views on treatment is essential to tackling polypharmacy and inappropriate prescribing.

The SPPiRE intervention provides structure and assistance in performing medication reviews by aiding GPs in identifying PIP, suggesting alternatives and encouraging care to be tailored to individual patient priorities. Strengths of this study include the pragmatic study design, incorporation of clinical guidelines and the fact that the intervention can be delivered by the patient’s GP. Currently, there is no provision under the GP reimbursement scheme in Ireland for a medication review for older patients and the potential and costs of a system-wide implementation of the SPPiRE intervention in Irish primary care will be explored in the process and economic evaluations.

Limitations of the study include the possibility of contamination of the control group where GPs also identify patients on 15 or more medicines using the patient finder tool and may treat these patients differently or provide more consideration than usual when renewing prescriptions. This will be explored in the process evaluation. Patients will also be encouraged to think about their treatment burden and attitudes towards deprescribing when completing baseline questionnaires and may be influenced to discuss their medications with their GP. Secondly, given the nature of the intervention it is not possible to blind patients, GPs or study personnel to the intervention. This has been addressed somewhat by using robust, objective primary outcome measures where there is little room for subjective opinion (number of repeat medicines and number of patients with any pre-defined PIP).

In summary, this study will provide evidence on the effectiveness and acceptability of a complex intervention designed to support GPs improve prescribing and reduce polypharmacy for older patients with multimorbidity and significant polypharmacy in Irish primary care.

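### Practice reporting and causality assessment of harms are worded for stopped medicines only, although the review also starts and substitutes medicines

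*Protocol article*

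**What the plan says.** Under Monitoring and participant safety, the protocol article states: "A formal process has been developed to capture any potential adverse events related to discontinuing medication". The instruction to practices has the same scope: "Recruited practices will be instructed in the practice recruitment leaflet on how to report any suspected adverse effects from deprescribing". The one causality method named is also a withdrawal method: "An assessment on likely causality will then be made using an adapted drug withdrawal probability scale". The patient-reported safety outcome, listed under Outcomes measures, is the adverse drug withdrawal event, "defined as either recurrence of the condition for which the drug was prescribed or a physiologic reaction to drug withdrawal".

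Two statements in the safety section are broader. One concerns data collection: "Any adverse events will also be captured by a chart review at follow-up data collection". The other sends "Any patient safety concerns arising during the course of the trial" to the Trial Steering Committee.

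The Discussion describes the intervention as a medication review "where deprescribing is considered alongside prescribing".

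**The concern.** The stated scope of harm reporting is narrower than the intervention it is meant to monitor. A GP who follows the review may stop a drug, replace it with another, or add one. The leaflet instruction, as described, asks practices to report suspected harm from the first of these only. The named causality method likewise refers to withdrawal.

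At stake is how soon, and how well, a reaction to a drug begun at the review is recognised as such. Under the text as written, a practice has no stated prompt to report that reaction when it occurs, and no stated method for judging whether the new drug caused it. The trial's Background itself names adverse drug reactions, and the prescribing cascades they set off, as central problems of polypharmacy. Harms of drugs started therefore belong in the safety account alongside harms of drugs stopped.

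**Working it through.** No power or error-rate calculation applies. The check sets the scope of the safety process beside the scope of the intervention.

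**1. Does the review start or substitute medicines?** Yes, according to several sections:
- Rationale for SPPiRE trial: inappropriate medicines may be changed as well as discontinued.
- The intervention: GPs consider suggested treatment alternatives for each problem found. Not all of these need be drugs.
- Outcomes measures: the number of medicines started is a secondary outcome, compared by arm.
- Process evaluation data collection: a decision to start a medicine is one of the recorded decisions.
- Discussion: prescribing and deprescribing are considered together.

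**2. Do the criteria themselves point to adding drugs?** Count of rows by drug group:
- Table 2: NSAIDs 8 + antiplatelets 4 + anticoagulants 4 + diuretics 4 = 20.
- Table 3: anticholinergics 4 + benzodiazepines or Z drugs 1 + antipsychotics 1 = 6.
- Table 4: methotrexate 2 + opioids 1 + corticosteroids 1 + PPI 1 + metformin 1 = 6.
- Total: 20 + 6 + 6 = 32.
- Rows defined by an absent protective drug: 3 NSAID and 3 antiplatelet rows without gastroprotection, 1 opioid row without a laxative, 1 corticosteroid row without bone protection. 3 + 3 + 1 + 1 = 8, and 8/32 = 25%.

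Adding a drug is one direct way to resolve these 8 rows, though some could also be resolved by stopping the drug that creates the risk. This is a share of criteria. It is not a share of patients or of prescribing decisions.

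**3. Which stated safety routes reach a reaction to a started or substituted drug?**

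| Route | Stated scope | Reaches it? |
|---|---|---|
| Formal process | Discontinuing medication | Not as worded |
| Practice leaflet instruction | Deprescribing | Not as worded |
| Named causality method | Withdrawal scale | No method named for started drugs |
| Patient-reported outcome | Withdrawal events | Recurrence of the original condition after a switch: yes. New reaction to the replacement: no |
| Chart review | Any adverse event | Yes, at follow-up |
| Steering committee | Any safety concern | Yes, if someone raises it |

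**4. When does the chart review happen?** For intervention patients, "Follow-up data will be collected 6 months following completion of each medication review in intervention patients". A reaction soon after the review may therefore first be recorded months later, unless it is raised as a safety concern in the meantime.

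The residue is two items: the practice instruction, and the attribution of events after a started or substituted drug.

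**The case against.** The strongest reply is that this is a condensed article, that the leaflet is not shown, and that describing a process for discontinuation events does not exclude other events. The chart review and the steering committee route are both worded without restriction, and the second operates during the trial. Emergency admissions with reasons, A&E visits and EQ-5D-5L also allow overall harm to be compared by arm. A focus on withdrawal is defensible as well: the aim is to reduce inappropriate prescribing and polypharmacy, and the pilot showed a net fall of 17.5 − 16.8 = 0.7 medicines.

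Much of this stands. It rules out the stronger inference that harms of started drugs go uncaptured, because the chart review covers them. It also supports withdrawal as the main focus. It does not remove the mismatch, because the article is not silent here: it states the scope of the process, the content of the practice instruction and the causality tool, and all three concern stopping. A net fall in medicines does not mean that none were started.

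A reader might also infer that the withdrawal scale would be applied to every event found at chart review and would misclassify reactions to new drugs. The documents do not support that. The causality sentence can be read as belonging to the discontinuation process that opens the paragraph, and the items of the adapted scale are not shown. What can be said is that no other method is named.

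**Conclusion.** The point holds in a narrow form and is minor. The stated reporting scope does not match the intervention. If followed as written, it gives later and less complete practice reporting, and no named attribution method, for events after a started or substituted drug.

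Its size cannot be estimated. The pilot reviewed 10 patients and does not report how many drugs were started or substituted, so a projected number of added drugs or reactions would have no sound basis. No primary outcome is affected.

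The conclusion assumes that the leaflet and the full safety procedures match the article's description. If the leaflet already asks for suspected reactions to any medication change, only the article's wording and the causality method remain to be settled.

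**What to change.** In the safety section and the practice leaflet, for both arms, replace the references to discontinuing medication and to deprescribing with any medication change, whether a drug is stopped, started or substituted. Keep the adapted withdrawal scale for events after a stopped drug. Assess events after a started or substituted drug with a standard adverse drug reaction causality scale. Report both counts by arm descriptively, without a test, and state that assessment was unblinded.

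The cost is a wording change and a second short causality form. No new visits or data sources are needed, since the chart review and the counts of medicines started and stopped are already planned. The downside is slightly more classification work. Attribution in patients on 15 or more medicines is also subjective, so the counts should not carry more than descriptive weight.
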